### **7.5.1 Product Supply**

As this is a Post-Marketing observational program, the Sponsor will not be involved in the product supply since the Betaserc® is being used according to the approved marketing authorization in the respective countries and is to be prescribed by the physician under usual and customary practice of physician prescription.

### **7.5.2 Description of Activities**

#### **Visit 1, Baseline / Start of therapy:**

Following activities will be performed:

- Sign and Date of Patient Authorization (Consent) for Use/Disclosure of Data.
- Check inclusion/exclusion criteria
- Collect demographic data
- Register date of start of betahistine dihydrochloride (Betaserc®) treatment (can differ from enrollment date, please see section 7.1.1)
- Register concomitant medication

[figure not shown]

- Collect medical history
- Allocation of patient identification number
- Performed routine physical examination including vitals (heart rate, systolic and diastolic blood pressure)
- Collect specific underlying ICD-10 diagnosis account for Vestibular Vertigo
- Register of the number of vertigo attacks for the previous month
- Evaluate patient's clinical conditions based on SVVSLCRE
- SAE monitoring

**Visit 2, up to 30th day from the first dose of Betaserc®:**

The following procedures will be performed:

- Register concomitant medication
- Evaluate patient's clinical conditions based on SVVSLCRE
- Register of the number of vertigo attacks for the previous month
- Assess overall clinical response and clinical response as improvement of vestibular vertigo associated symptoms based on four-point scale
- SAE monitoring

**Visit 3, up to 60th day from the first dose of Betaserc®, End of Observational Treatment Period / Early Termination:**

The following procedures will be performed:

- Register concomitant medication
- Evaluate patient's clinical conditions based on SVVSLCRE
- Register of the number of vertigo attacks for the previous month

[figure not shown]

- Assess overall clinical response and clinical response as improvement of vestibular vertigo associated symptoms based on four-point scale
- SAE monitoring

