#### **6.4 Secondary Endpoints**

1. Number and proportion of patients in each category of SVVSLCRE at baseline and end of observational treatment period in patients who completed betahistine treatment over a period less or equal 30 days and in patients who completed betahistine treatment over a period more than 30 days but less or equal 60 days.
2. Change of the patient's clinical conditions of vestibular vertigo assessed with SVVSLCRE from baseline to the end of observational treatment period in patients who completed betahistine treatment over a period less or equal 30 days and in patients who completed betahistine treatment over a period more than 30 days but less or equal 60 days.
3. Change of the patient's clinical conditions of vestibular vertigo assessed with SVVSLCRE from baseline to Visit 2 in patients who completed betahistine treatment over a period more than 30 days but less or equal 60 days.

[figure not shown]

4. Change of vestibular vertigo attacks frequency from baseline to the end of observational treatment period in patients who completed betahistine treatment over a period less or equal 30 days and in patients who completed betahistine treatment over a period more than 30 days but less or equal 60 days.
5. Change of vestibular vertigo attacks frequency from baseline to Visit 2 in patients who completed betahistine treatment over a period more than 30 days but less or equal 60 days.
6. Overall clinical response assessed by physician will be determined based on a four-point-scale, where 4 = excellent, 3 = good, 2 = fair, and 1 = poor. Proportion of patients in each category at the end of observational treatment period will be determined in patients who completed betahistine treatment over a period less or equal 30 days and in patients who completed betahistine treatment over a period more than 30 days but less or equal 60 days. Proportion of patients in each category at Visit 2 will be determined in patients who completed betahistine treatment over a period more than 30 days but less or equal 60 days.

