#### **7.1.1 Inclusion Criteria**

1. Male or female with age  $\geq 18$  years.
2. Patients with vestibular vertigo of known or unknown origin, and for whom the physician has decided to prescribe 48 mg of betahistine dihydrochloride (Betaserc®) in accordance with locally approved label.
3. Patients who are willing and able to provide authorization to the investigator to use and/or disclose personal and/or health data.
4. Patients who started betahistine dihydrochloride (Betaserc®) therapy not more than 5 days prior to sign Patient Authorization (Consent) for Use/Disclosure of Data.

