## **7.5 Program Conduct**

The patient visits will be scheduled based on routine practice of the physician. 60 days of observational treatment period has been chosen as a length of time sufficient to generate useful effectiveness data. Follow-up visits for this program has been recommended keeping in mind the treating physician's usual pattern of follow-up consultations.

To optimize data collection, three visits are indicated within approximately 2 months of observational treatment period and two visits within approximately 2 months of follow-up period:

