### *I. Observational treatment period*

**Visit 1:** Baseline/Start of therapy

**Visit 2:** up to 30th day from the first dose of Betaserc®

**Visit 3:** up to 60th day from the first dose of Betaserc®, End of observation treatment period / Early Termination

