**Figure 2: Overall Investigational Plan of Study**

[figure not shown]

[figure not shown]

Table 2 Program Activities

| Weeks of Treatment                                                                                                                               |                        | Observational treatment period                                        |                                                                                   | Evaluation of the course of vestibular vertigo in follow-up period |                                                           |
|--------------------------------------------------------------------------------------------------------------------------------------------------|------------------------|-----------------------------------------------------------------------------------|-----------------------------------------------------------------------------------|--------------------------------------------------------------------|-----------------------------------------------------------|
|                                                                                                                                                  | Visit 1                | Visit 2                                                                           | Visit 3                                                                           | Visit 4                                                            | Visit 5                                                   |
|                                                                                                                                                  |                        | Expected up to 30 th day from the first dose of Betaserc®  | Expected up to 60 th day from the first dose of Betaserc®  | 30 th (±7) day from the last dose of Betaserc®          | 60 th (±7) day from the last dose of Betaserc® |
|                                                                                                                                                  | Screening/
Baseline |                                                                                   | End of observational treatment period  /Early termination           |                                                                    | End of follow-up period                                   |

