| Overall clinical response and clinical response as improvement of vestibular vertigo associated symptoms based on four-point scales  |                        | X                                                                                 | X                                                                                 |                                                                    |                                                           |
| SAE monitoring                                                                                                                       | X                      | X                                                                                 | X                                                                                 | X                                                                  |                                                           |

 This program does not include patients who required betahistine therapy, according to physician's decision, more than 60 days.

 Actual date of visit may be up to 7 days from the last betahistine dose, otherwise proceed to Visit 4.

[figure not shown]

 This coincides with Visit 2 in case patient had completed betahistine treatment period lasting 30 days or less. In case physician decides to continue betahistine therapy beyond 30 days, Visit 3 will be a separate visit from Visit 2.

 For patients whom physician decides to continue betahistine therapy beyond 60 days treatment course, no follow up will be done and end of observational treatment period will denote end of program.

 Includes sex, age, race (white, black, asian, other), weight and height

 Heart rate, blood pressure (systolic and diastolic)

 for more detailed information about Scale for Vestibular Vertigo Severity Level and Clinical Response Evaluation please see section 6.3, Figure 1 and Table 1.

 Four-point-scale, where 4 = excellent, 3 = good, 2 = fair, and 1 = poor.

 30 days after end of program treatment or early termination, a telephone call will be made to enquire about development of any SAE. If there is a positive feedback, relevant medical history and adverse event details will be collected.

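### A fixed one-month attack count, taken at a visit that may fall before day 30, re-counts pre-treatment days and shrinks the recorded change in attack frequency

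*Protocol*

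**What the plan says.** Protocol section 7.5.2 has the same item at Visits 1 to 5: "Register of the number of vertigo attacks for the previous month". The length of a month is not defined.

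The timing around that item varies:

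- Section 7.5: "The patient visits will be scheduled based on routine practice of the physician". Visit 2 is "up to 30 th day from the first dose of Betaserc" and Visit 3, which also serves as early termination, is "up to 60 th day from the first dose of Betaserc". Neither has a lower limit.
- Table 2, footnote 3: if the course lasts 30 days or less, the end-of-treatment visit is Visit 2.
- Table 2, footnote 2, for Visits 2 and 3: "Actual date of visit may be up to 7 days from the last betahistine dose, otherwise proceed to Visit 4".
- Section 7.1.1, criterion 4, admits "Patients who started betahistine dihydrochloride (Betaserc®) therapy not more than 5 days prior to sign Patient Authorization (Consent) for Use/Disclosure of Data". Visit 1 can therefore come up to 5 days after the first dose.
- Table 2 sets Visits 4 and 5 at 30 ± 7 and 60 ± 7 days after the last dose.

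The endpoints are in section 6.4. Item 4 is "Change of vestibular vertigo attacks frequency from baseline to the end of observational treatment period in patients who completed betahistine treatment", given separately for courses of at most 30 days and of 31 to 60 days. Item 5 compares baseline with Visit 2 in the longer-course group. Items 10 and 11 compare the end of treatment with months 1 and 2 of follow-up in both groups. Section 11.0 analyses the number of monthly attacks with paired tests. Nothing in the protocol ties the count to the first dose, the last dose or the previous visit.

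**The concern.** A baseline-to-treatment comparison needs one window before the first dose and one after it. A one-month look-back from a visit on day 14 reaches 16 days back beyond the first dose, into days that the baseline count already covers. If attacks fall on treatment, the recorded fall is too small, by an amount set by when the clinic happened to see the patient.

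For items 10 and 11 the error can change direction. An end-of-treatment reference inflated by pre-treatment days makes follow-up look better than it is. That matters because secondary objective 2, the post-treatment course, rests on attack counts alone: the severity scale and the response ratings stop at Visit 3.

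This is not a detail that can wait for an analysis plan. Once a single number has been entered for the past month, it cannot be divided at the first dose.

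**Working it through.** The protocol gives no figure for attack frequency, so there is none to reproduce. Its only calculation, for the primary proportion, does reproduce (1.96² × 0.80 × 0.20 / 0.05² = 245.9, so 246; 246 / 0.80 = 307.5, so 308) but does not bear on this point.

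**Assumptions.** A month is 30 days. The attack rate is constant before, during and after treatment, with a step at the first and at the last dose. The documents give no distribution of visit days, so a range is shown.

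**Visit 2, or the end visit of a short course.** Let d be the visit day after the first dose and b the number of days from first dose to Visit 1 (0 to 5).

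- Pre-treatment days in the window = max(0, 30 − d).
- Fraction of a true change recorded = (min(d, 30) − b) / 30.

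| d | pre-treatment days | recorded, b = 0 | recorded, b = 5 |
|---|---|---|---|
| 7 | 23 | 23% | 7% |
| 14 | 16 | 47% | 30% |
| 21 | 9 | 70% | 53% |
| 28 | 2 | 93% | 77% |
| 30 | 0 | 100% | 83% |

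**End visit on day 31 or later (31-to-60-day group).** There are no pre-treatment days in the window. The only loss in item 4 from treated baseline days is b/30, so 83% to 100% is recorded.

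**Follow-up.** Let g be the days from last dose to end visit (0 to 7) and f the days from last dose to Visit 4 (23 to 37).

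- Treated days in the Visit 4 window = max(0, 30 − f), at most 7.
- Fraction of a true post-treatment change recorded = (min(f, 30) − g) / 30. For f = 23 this is 77% with g = 0 and 53% with g = 7. For f = 30 and g = 7 it is 77%.
- An end visit at +7 covers days −23 to +7 around the last dose. Visit 4 at +23 covers −7 to +23. They share 14 of 30 days, the maximum.
- Visit 5 (days 53 to 67) contains no treated days. Item 11 is touched only through its reference value: (30 − 7) / 30 = 77% at g = 7.

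**Illustration** with assumed rates of 10 attacks per month before treatment and 4 on treatment (true change −6.0), b = 0:

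- Day 14: (16 × 10 + 14 × 4) / 30 = 7.2, recorded change −2.8.
- Day 21: (9 × 10 + 21 × 4) / 30 = 5.8, recorded change −4.2.
- Day 30: 4.0, recorded change −6.0.

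If the rate stays at 4 after treatment, those day-14 and day-21 references give spurious further falls of 3.2 and 1.8. If the rate instead rose from 4 to 7.2, the day-14 reference would show no change.

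**The case against.** A uniform one-month recall is a defensible unit in a non-interventional programme where visits follow routine care. The overlap with the pre-treatment month is possible rather than certain, and it vanishes for a visit on day 30. Section 11.0 says that p-values and intervals for secondary endpoints are descriptive and not for inference. For items 4 and 5 the bias is toward no change if attacks fall. All of this stands and limits the weight of the point. It does not remove it: the plan sets no lower limit on visit day, and section 11.0 still labels results at p ≤ 0.05 as statistically significant.

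Several stronger readings are tempting, but the documents do not support them:

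- *That every attack endpoint is diluted in every patient.* In the 31-to-60-day group an end visit on day 31 or later cannot reach the pre-treatment month, and Visit 5 holds no treated days.
- *That items 10 and 11 are badly affected by very short courses.* Sections 7.4 and 7.5 restrict follow-up to patients finishing in 1 to 2 months, while section 6.4 (items 10 and 11) and section 11.0 (item 10) include the group treated for 30 days or less. How many short-course patients contribute is unclear.
- *That the variable spacing of Visits 4 and 5 is a fault.* No endpoint compares these two visits.
- *That Russia and Ukraine become non-comparable.* Nothing indicates that visit timing differs between them.
- *That the comparison of the two duration groups is invalid.* No between-group test is planned.

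**Conclusion.** The point holds in a limited form. Where Visit 2, or an end or early-termination visit, falls before day 30, the attack count includes pre-treatment days already counted at baseline, and about d/30 of a true change is recorded, less if Visit 1 followed the first dose. This concerns endpoint 5, endpoint 4 in the group treated for 30 days or less, and that group's reference value for endpoints 10 and 11 as far as those patients enter follow-up. There it can produce a spurious further fall or hide a return of attacks.

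In both groups there is smaller contamination: up to 5 treated days in the baseline window, up to 7 off-treatment days in the end-visit window and up to 7 treated days in the Visit 4 window.

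The percentages rest on the 30-day month, constant rates and step changes; the rates of 10 and 4 are illustrative only. The realised size depends on visit days that the documents do not give. The primary endpoint and sample size are untouched. The change should be made before data collection because the loss cannot be recovered afterwards, but it is not a fatal flaw.

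**What to change.** In section 7.5.2 and Table 2:

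- Record the last-dose date explicitly; Table 2 lists only the start date.
- Visit 1: count attacks in the 30 days before the first dose.
- Visit 2, and any end or early-termination visit before day 30: count from the first dose to the visit or the last dose, whichever is earlier, and scale to 30 days (30 × count / days in the interval).
- Visit 3 on day 30 or later: count the 30 days ending at the visit or the last dose, whichever is earlier. If the time since the first dose is shorter than that, count from the first dose and scale.
- Visit 4: count from the last dose to the visit (23 to 37 days) and scale to 30 days.
- Visit 5: keep the previous 30 days.

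Use these rates for endpoints 4, 5, 10 and 11 in section 11.0. Counting simply since the previous visit would be worse: Visit 2 on day 30 and Visit 3 on day 35 would replace a clean 30-day window with a 5-day count multiplied by 6.

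The cost is new eCRF labels, one date field and a simple derivation. Rates from short intervals will be noisier, some recall periods will end a few days before the visit, and the Visit 4 interval can run to 37 days.

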**Visit 4, 30th ( $\pm 7$ ) day from the last dose of Betaserc®:**

- Register concomitant medication
- Register of the number of vertigo attacks for the previous month
- SAE monitoring

**Visit 5, 60th ( $\pm 7$ ) day from the last dose of Betaserc®:**

- Register concomitant medication
- Register of the number of vertigo attacks for the previous month

## **8.0 Adverse Events**

### **8.1 Adverse Event Definition and Serious Adverse Event Categories**

An adverse event (AE) is defined as any untoward medical occurrence in a patient, which does not necessarily have a causal relationship with their treatment. An adverse event can therefore be any unfavorable and unintended sign (including an abnormal laboratory finding), symptom, or disease temporally associated with the use of a medicinal product, whether or not the event is considered causally related to the use of the product.

Such an event can result from use of the drug as stipulated in the labeling, as well as from accidental or intentional overdose, drug abuse, or drug withdrawal. Any worsening of a pre-existing condition or illness is considered an adverse event.

[figure not shown]

If an adverse event meets any of the following criteria, it is considered a **serious adverse event (SAE)**:

|                                                                                                       |                                                                                                                                                                                                                                                                                                                                                                                                                                                                                                                                                                                                                                                                                                                                                                                                                  |
|-------------------------------------------------------------------------------------------------------|------------------------------------------------------------------------------------------------------------------------------------------------------------------------------------------------------------------------------------------------------------------------------------------------------------------------------------------------------------------------------------------------------------------------------------------------------------------------------------------------------------------------------------------------------------------------------------------------------------------------------------------------------------------------------------------------------------------------------------------------------------------------------------------------------------------|
| Death of Subject:                                                                              | An event that results in the death of a subject.                                                                                                                                                                                                                                                                                                                                                                                                                                                                                                                                                                                                                                                                                                                                                                 |
| Life-Threatening:                                                                              | An event that, in the opinion of the investigator, would have resulted in immediate fatality if medical intervention had not been taken. This does not include an event that would have been fatal if it had occurred in a more severe form.                                                                                                                                                                                                                                                                                                                                                                                                                                                                                                                                                                     |
| Hospitalization:                                                                               | An event that results in an admission to the hospital for any length of time. This does not include an emergency room visit or admission to an outpatient facility.                                                                                                                                                                                                                                                                                                                                                                                                                                                                                                                                                                                                                                              |
| Prolongation of Hospitalization:                                                               | An event that occurs while the study subject is hospitalized and prolongs the subject's hospital stay.                                                                                                                                                                                                                                                                                                                                                                                                                                                                                                                                                                                                                                                                                                           |
| Congenital Anomaly:                                                                            | An anomaly detected at or after birth, or any anomaly that results in fetal loss.                                                                                                                                                                                                                                                                                                                                                                                                                                                                                                                                                                                                                                                                                                                                |
| Persistent or Significant Disability/Incapacity:                                               | An event that results in a condition that substantially interferes with the activities of daily living of a study subject. Disability is not intended to include experiences of relatively minor medical significance such as headache, nausea, vomiting, diarrhea, influenza, and accidental trauma (e.g., sprained ankle).                                                                                                                                                                                                                                                                                                                                                                                                                                                                                     |
| Important Medical Event Requiring Medical or Surgical Intervention to Prevent Serious Outcome: | An important medical event that may not be immediately life-threatening or result in death or hospitalization, but based on medical judgment may jeopardize the subject and may require medical or surgical intervention to prevent any of the outcomes listed above (i.e., death of subject, life threatening, hospitalization, prolongation of hospitalization, congenital anomaly, or persistent or significant disability/incapacity). Additionally, any elective or spontaneous abortion or stillbirth is considered an important medical event. Examples of such events include allergic bronchospasm requiring intensive treatment in an emergency room or at home, blood dyscrasias or convulsions that do not result in inpatient hospitalization, or the development of drug dependency or drug abuse. |

[figure not shown]

